**Discussion:**

CorLipid is an ongoing trial aiming to investigate the correlation between metabolic profile and complexity of coronary artery disease in a cohort of patients undergoing coronary angiography with the potential to suggest a decision-making tool with high discriminative power for patients with CAD. To our knowledge, Corlipid is the first study aspiring to create an integrative metabolomic biomarkers-based algorithm by combining metabolites from multiple classes, involved in a wide range of pathways with well-established biochemical markers.

*Trial registration* CorLipid trial registration: ClinicalTrials.gov number: NCT04580173. Registered 8 October 2020—Retrospectively registered, https://clinicaltrials.gov/ct2/show/NCT04580173.

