### Statistical considerations

#### Sample size estimation

Sample size estimation for studies utilizing metabolomic data in various degrees is not straightforward as effect sizes are not readily established in this very active area of research. The primary endpoint of the study is to discover potential correlations of clinical types of Coronary Artery Disease with patients' metabolic profile. Syntax score as a descriptor of CAD complexity could be probably correlated with an array of known and novel small molecule biomarkers to determine if the varying level of CAD complexity is related to metabolism.

Targeted analyses on concentrations of known molecules, such as Ceramides, Galectin-3, Adiponectin, NGal etc. will be the majority of the metabolic profile analyses conducted and we intent to explore potential correlations of them with the Syntax score. This multiparametric approach hinders a more accurate estimation of an effect size, as there is a multitude of factors at play. Thus, using a pilot study of 100 patients, we performed a linear multiple regression random model to establish an effect size for a direct effect on the SYNTAX score from various parameters. In this pilot study we chose 10 predictors (concentrations of current and potential biomarkers and categorical parameters) as in the expanded study we will aim to choose smaller more concise models with less than 10 predictors of better biological interpretations.

Using the G*Power tool [17] and a calculated effect based on a regression model R^2^ of 0.370, an effect size of H1 p^2^ 0.30 was yielded. We expect other factors, not explicitly measured by this study, to also independently influence CAD complexity as measured by Syntax score, so we arbitrary assume a Η0 ρ^2^ of 0.20. So for an A of 0.01 and a Power of 0.95 a sample size of 1014 is sufficient. This initial sample size will be increased by 5%, as some study participants might be lost to follow-up. Hence, we aim for a total of 1065 patients.

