### Statistical analysis

Normally distributed data will be analyzed using parametrical tests, such as Student *t*-test and for non-normally distributed data nonparametric test such are Mann–Whitney and multiparametric Kruscal-Wallis H test will be utilized, as indicated by the Kolmogorov-Smirnoff Test for normality. Categorical variables will be compared using the χ^2^ test. Continuous data will be presented as mean ± SD, whereas categorical variables will be displayed as counts and percentages. Univariable, multivariable and correlations analysis will be carried out to clarify independent predictors of various CAD characteristics, biochemical measurements and associations with SYNTAX score, metabolic biomarkers individually as well as follow up MACCE.

Linear and logistic regression, using stratified bootstrapping if needed to account for potential non-parametric data, will be used to identify independent predictors of CAD characteristics and Syntax Score. Receiver operating characteristic (ROC) curve analysis -and derived area under the curve (AUC) -will be utilized when appropriate. Cox regression analyses and Kaplan–Meier survival will be calculated for the 1 year follow-up for Syntax score groups and to check the validity of potential predictive models that will emerge, with the difference between different patient sub-groups analyzed by the log-rank test. Patients that are lost to follow-up will be censored at their last study encounter. The level of statistical significance will be considered at a = 0.05 and every statistical test will be performed via SPSS v. 26.

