#### Endpoints

The study primarily aims to combine clinical characteristics with established and novel biomarkers, in order to develop a risk prediction model, which could optimally identify patients at high risk for CAD and most importantly, patients at high risk for complex CAD based on their metabolite signatures.

A secondary endpoint of this study is the identification of a biomarkers’ panel for the distinction of acute from chronic coronary syndromes by detecting metabolite pattern differences. Finally, all patients will be followed-up via telephone for 12 months for any MACCE to develop a new prognostic metabolomics-based model for CAD patients (Fig. 1).

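### The validity check that the article names (Cox and Kaplan-Meier in the same cohort) does not validate the prediction models, so an AUC obtained as written would be optimistic

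*Protocol article*

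**What the plan says.** All of this is in the protocol article.

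- **Aim.** The Endpoints section sets out to "develop a risk prediction model, which could optimally identify patients at high risk for CAD", and above all those at high risk of complex CAD. The abstract's Discussion looks toward a "decision-making tool with high discriminative power for patients with CAD", worded there as a potential outcome and not a promise.
- **Choice of predictors.** Sample size estimation reports a 10-predictor pilot model in 100 patients. It leaves the final models, with fewer than 10 predictors, to be chosen in the expanded study.
- **Candidates.** Biochemical analysis-metabolomics lists four ceramides with their ratios, fifteen acylcarnitines, total fatty acids, four protein markers, and an untargeted panel of unstated size.
- **Analysis.** Statistical analysis uses univariable, multivariable, linear and logistic regression to find predictors, with ROC curves and AUC where appropriate. Bootstrapping appears once: "using stratified bootstrapping if needed to account for potential non-parametric data".
- **Validity.** The same section applies Cox and Kaplan-Meier methods to the 1-year follow-up, by SYNTAX group and "to check the validity of potential predictive models that will emerge".
- **Follow-up data.** Endpoints uses the 12-month MACCE follow-up of all patients to develop the prognostic model.

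**The concern.** A model whose predictors are picked and whose coefficients are fitted in one set of patients discriminates better in those patients than in new ones. Validation has to measure that gap or remove it. The step that the article calls a validity check does neither, and no other named step does.

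At stake is how the main deliverable is read. If the AUC is reported as obtained, readers cannot tell how much of it would survive in new patients. The risk is greatest where events are few and candidate markers many, which fits the highest SYNTAX class and probably MACCE.

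**Working it through.** **1. The plan's own figure.** The sample size section states "So for an A of 0.01 and a Power of 0.95 a sample size of 1014 is sufficient", with "a calculated effect based on a regression model R^2^ of 0.370, an effect size of H1 p^2^ 0.30 was yielded" and "so we arbitrary assume a Η0 ρ^2^ of 0.20". Under the exact distribution of R² with random predictors (H0 ρ² = 0.20, H1 ρ² = 0.30, 10 predictors, α = 0.01, power 0.95), the two-sided N is 1014, an exact match; the one-sided N is 900. Then 1014 × 1.05 = 1064.7, giving 1065. The figure reproduces, but it powers a test of ρ² and does not address performance in new patients.

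**2. What the named check can do for each model.**

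| Model | Outcome developed on | Outcome in Cox/Kaplan-Meier | Patients | Result |
|---|---|---|---|---|
| SYNTAX (complex CAD) | SYNTAX score or group | 12-month MACCE | same cohort | shows prognostic association; cannot verify or correct the AUC |
| ACS versus chronic syndromes | presentation | 12-month MACCE | same cohort | as above |
| MACCE prognostic model | 12-month MACCE | 12-month MACCE | same cohort | re-uses the development data |

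**3. Projected events.** Table 2 has 72 patients with SYNTAX 23–32 and 34 above 32, out of 596.

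- Above 32: 34/596 × 1065 = 60.8, about 61 (about 58 at N = 1014).
- Above 22: (72 + 34)/596 × 1065 = 189.4, about 189 (about 180 at N = 1014).

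**4. Size of the optimism, by simulation.** Optimism = AUC in the development patients − AUC in new patients. Setting: N = 1014, 200 replicates, independent standard-normal markers, the nine strongest univariably entered in a logistic model, five true markers with log odds ratio 0.3 per SD. From the documents come N, the event proportions and the limit of fewer than 10 predictors. Marker effects, independence, the selection rule and the candidate counts (40 for a targeted pool, 300 with untargeted features) are assumptions.

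| Outcome | 9 fixed | 40 candidates | 300 candidates |
|---|---|---|---|
| SYNTAX > 22 | 0.687 − 0.666 = 0.021 | 0.703 − 0.652 = 0.051 | 0.719 − 0.629 = 0.090 |
| SYNTAX > 32 | 0.706 − 0.653 = 0.053 | 0.744 − 0.616 = 0.128 | 0.790 − 0.568 = 0.222 |
| ACS versus chronic | 0.680 − 0.668 = 0.012 | 0.692 − 0.659 = 0.033 | 0.701 − 0.649 = 0.052 |

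A repeat at N = 1065 gave 0.022, 0.048 and 0.089 for SYNTAX > 22, and 0.054, 0.121 and 0.211 for SYNTAX > 32.

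**5. MACCE.** The article gives no event rate, so 5%, 10% and 15% were assumed (51, 101 and 152 events of 1014, treated as binary). Optimism was about 0.14, 0.08 and 0.06 with 40 candidates, and about 0.24, 0.15 and 0.11 with 300.

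**6. Worst case, no true signal.** AUC in new patients is 0.50. The development-patient AUC with 9, 40 and 300 candidates is 0.57, 0.62 and 0.67 for SYNTAX > 22, and 0.61, 0.69 and 0.77 for SYNTAX > 32.

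**7. The continuous score.** For linear regression at N = 1065 with assumed ρ² = 0.30, R² in development versus new patients was 0.305 versus 0.292 (9 fixed), 0.311 versus 0.289 (40 candidates, 5 true) and 0.316 versus 0.279 (500 candidates, 5 true). The optimism is 0.013, 0.022 and 0.037.

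**The case against.** **The article condenses a fuller plan.** Resampling details are commonly left to the full protocol or SAP, and silence alone would be no finding. That is fair, but the article is not silent: it names a validity procedure, and that procedure cannot do the job.

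**The clause may mean prognostic validity.** Asking whether a SYNTAX-based model also separates patients by later MACCE is reasonable. This stands as a use for the analysis, but it says nothing about discrimination for complex CAD, and for the MACCE model it is circular.

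**Stronger readings that the article does not support.**

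- A reader might infer that the plan commits to reporting an uncorrected AUC from the development patients. It never says so. The inference rests on there being one cohort and no named split, cross-validation or correction.
- A reader might infer that the Cox/Kaplan-Meier step itself inflates the SYNTAX AUC. It does not; it simply leaves that AUC unchecked.
- A reader might take the pure-noise AUCs as the expected result. They are a worst case. The pilot R² of 0.370, and the 0.30 used for planning, suggest some signal.
- A reader might take SYNTAX above 32 as the definition of complex CAD. The article does not fix a cut-off, and its sample size rests on linear regression of the score, where optimism is modest (step 7).

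**The simulation is a construction.** The article gives no selection algorithm or candidate count, says that targeted analyses will be the majority, and many of these markers are likely correlated, which lowers the effective number of candidates. All of this limits the size, not the direction.

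**Conclusion.** The point holds in this form: the stated validity check is not validation, and nothing else named in the article corrects for choosing and fitting predictors in the same patients. The table comparison in step 2 needs no assumption.

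The amount of overstatement is not fixed by the documents. Under the assumptions in step 4 it is small for predictors fixed in advance (about 0.01 to 0.05 in AUC). With selection from 40 candidates it is about 0.03 to 0.13 across the SYNTAX and ACS models. With 300 candidates it reaches 0.21 to 0.22 for SYNTAX above 32. For MACCE it depends on an event rate that the article does not give. The correction is cheap and belongs in the plan before the models are built.

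**What to change.** Replace the validity clause in Statistical analysis with the following:

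1. Internal validation by bootstrap or repeated cross-validation, with the whole marker selection, including any univariable screening, repeated inside each resample.
2. For the SYNTAX, ACS-versus-chronic and MACCE models, report the optimism-corrected AUC (R² if SYNTAX is modelled as continuous) and the calibration slope, next to the uncorrected figure.
3. Describe Cox and Kaplan-Meier as prognostic association with MACCE by predicted-risk group, not as a check of validity.

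The cost is extra analysis work and a lower reported AUC; no new patients or measurements are needed. Penalised regression, the SYNTAX cut-off and the software are optional choices that this fix does not depend on.

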### Biochemical analysis-metabolomics

Metabolomics-based analysis using Gas Chromatography tandem Mass Spectrometry (GC–MS) as well as targeted methods based on Liquid Chromatography tandem Mass Spectrometry (LC–MS) and Gas Chromatography with Flame Ionization Detector (GC-FID) will be performed. The untargeted approach will be used as it offers the advantages of novel biomarkers discovery from a wide range of compounds. The quantification of four ceramide species (C18:0/16:0, C18:0/18:0, C18:0/24:0 and C18:0/24:1) with their respective ratios and of fifteen short-, medium- and long chain acylcarnitines in serum CAD patients will be achieved with targeted methods by applying a developed RPLC and HILIC LC –MS/MS method, respectively. The composition of total fatty acids will be quantitatively measured in patients’ serum samples using a developed GC-FID based method. In addition, protein markers associated with CAD, namely Galectin-3, adiponectin, NGAL and ApoB/ ApoΑ-Ι will be measured by enzyme-linked immunosorbent assay (ELISA) in serum patients’ samples in order to enhance the predictive value of the CorLipid panel.

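### Marker-level tests on at least 23 analytes and several outcomes share one unqualified 0.05 level with no stated multiplicity control, while the study was sized on a single test at 0.01

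*Protocol article*

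**What the plan says.** The Statistical analysis section of the protocol article states the scope of the testing: "Univariable, multivariable and correlations analysis will be carried out to clarify independent predictors of various CAD characteristics". The same sentence goes on to SYNTAX score, to metabolic markers taken one at a time, and to MACCE at follow-up. The section closes with the level: "The level of statistical significance will be considered at a = 0.05". It draws no distinction between a primary test, the targeted markers and the untargeted features.

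The Biochemical analysis-metabolomics section fixes part of the number of tests. It lists four ceramide species with their ratios, fifteen acylcarnitines, a total fatty-acid composition, and four protein markers (galectin-3, adiponectin, NGAL and the ApoB/ApoA-I ratio). It adds a screen: "The untargeted approach will be used as it offers the advantages of novel biomarkers discovery from a wide range of compounds". The number of ratios, fatty acids and untargeted features is not given.

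The Sample size estimation section uses a different level for the only test it specifies, an overall multiple regression on SYNTAX score: "So for an A of 0.01 and a Power of 0.95 a sample size of 1014 is sufficient". For the final models it says: "in the expanded study we will aim to choose smaller more concise models with less than 10 predictors".

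**The concern.** A level of 0.05 is a reasonable error rate for one test. Applied to each of a few dozen markers, and then to each of several outcomes, it lets through a predictable number of null markers. The Endpoints section makes a risk prediction model the primary aim and a biomarker panel a secondary endpoint, so the list of markers that pass is close to the study's product. Null markers on that list would not be expected to replicate.

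The article also does not agree with itself on the level. The sample size was justified at 0.01 and the analysis is to be read at 0.05. A reader cannot tell which level decides the SYNTAX regression for which the study was sized.

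**Working it through.** **1. The plan's own figure.** Inputs from Sample size estimation: H0 rho² = 0.20, H1 rho² = 0.30, alpha 0.01, power 0.95, 10 predictors. Using the exact distribution of R² under the random-predictor model:

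- two-sided alpha 0.01 gives N = 1014 (power 0.9500), which matches the article; one-sided gives 900;
- 1014 × 1.05 = 1064.7, so 1065, which also matches.

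The same test at two-sided 0.05 would need 745. So the stated size belongs to one overall R² test at 0.01. It is not derived from marker-level tests at 0.05.

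**2. Countable markers.** 4 ceramides + 15 acylcarnitines + 4 proteins = 23. Ratios, fatty acids and untargeted features are left out because their numbers are not given.

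**3. False positives at 0.05 when every marker is null.**

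- Expected number per outcome: 23 × 0.05 = 1.15. This does not depend on correlation.
- Chance of at least one, independent tests: 1 − 0.95^23 = 0.693.
- Chance of at least one, correlated tests: simulated with equicorrelated normal test statistics (20,000 draws, two-sided 1.96).

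| Null tests | Expected false positives | Independent | Corr. 0.3 | Corr. 0.5 | Corr. 0.8 |
|---|---|---|---|---|---|
| 23 (one outcome) | 1.15 | 69% | 58% | 45% | 24% |
| 69 (23 × 3 outcomes) | 3.45 | 97% | 88% | 70% | 33% |
| 200 (assumed features) | 10 | >99.9% | 99% | 90% | 42% |
| 500 (assumed features) | 25 | about 100% | >99.9% | 99% | 51% |

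The 69-test row counts SYNTAX score, CAD characteristics (as one outcome) and MACCE.

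**4. Untargeted features.** The count is an assumption. Each 100 null features add 100 × 0.05 = 5 expected false positives per outcome, so 100 to 500 features add 5 to 25.

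**5. From screen to model.** For a model with 9 null predictors fixed in advance, the chance of at least one false positive at 0.05 is 1 − 0.95^9 = 0.37 (independent tests). The figures in step 3 carry over to such a model only if its predictors are picked from the screen.

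**6. Price of a stricter level.** Correlation detectable with 80% power at n = 1065, by Fisher's z: r = tanh((z_alpha + 0.842)/√1062).

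- p < 0.05: tanh((1.960 + 0.842)/√1062) = 0.086.
- p < 0.001: tanh((3.291 + 0.842)/√1062) = 0.126.

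The value 0.001 stands in for a false-discovery threshold, which depends on the data. For 23 markers the strictest Benjamini-Hochberg step is 0.05/23 = 0.0022, so 0.001 overstates the cost for that family. The calculation applies to a continuous outcome such as SYNTAX score, not to sparse binary outcomes.

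**The case against.** The strongest reply is that the article never says p-values will go unadjusted. The full sentence reads "The level of statistical significance will be considered at a = 0.05 and every statistical test will be performed via SPSS v. 26"; its second half concerns software, and a 0.05 level is compatible with adjusted p-values. A multiplicity procedure is also something an article may leave to an analysis plan that is not shown. This stands as far as it goes: the level is stated, the absence of adjustment is not. It does not remove the point, because the level that is stated carries no qualifier and differs from the one used for sizing.

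Several stronger readings are tempting and should not be drawn:

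- **That false independent predictors are virtually certain.** The countable markers give 69% on one outcome, and only if all are null and independent. Markers within one lipid class are plausibly correlated, which lowers the figure. Some may not be null: the proteins were chosen for a known link with CAD, the Discussion cites ceramide ratios as predictors of cardiovascular death, and the pilot R² was 0.370. Near-certainty needs several outcomes or many untargeted features, without strong correlation, and the feature count is not given.
- **That each analyte is tested singly for acute versus chronic disease.** The Endpoints section describes a panel and pattern differences for that comparison, not single-marker tests.
- **That null markers pass straight into the panel.** No rule admitting a marker on p < 0.05 is written, and models with fewer than 10 predictors are intended. Equally, no other selection rule is given.

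It is also fair to say that much of the study is discovery work, where the strictness of error control is partly a choice. That supports labelling results as exploratory; it does not support reading every marker at the same 0.05 as the primary test.

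**Conclusion.** The point holds in a limited form. Followed as written, the article applies a single 0.05 level, with no multiplicity control stated, to marker-level analyses of at least 23 named analytes against several outcomes. The only test for which the study was sized used 0.01.

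The firm figure is 1.15 expected false positives per outcome; it assumes that all 23 markers are null and that 0.05 is applied without adjustment. The chance of at least one depends on correlation as well: 69% under independence, about 45% at correlation 0.5. Any figure for the untargeted screen rests on an assumed feature count. The mismatch between 0.01 and 0.05 needs no assumption, since both values are printed in the article.

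**What to change.** In the Statistical analysis section, replace the blanket level with three statements:

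1. The primary SYNTAX regression model is tested at alpha 0.01, to match the sample size section.
2. Marker-level tests use Benjamini-Hochberg control of the false-discovery rate at 5% within each outcome, with targeted analytes and untargeted features as separate families.
3. Unadjusted results below 0.05 are labelled exploratory and are not used alone to declare a predictor.

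This takes one paragraph and a routine adjustment; recruitment, assays and sample size do not change. The downside is fewer nominally significant metabolites and some loss of power. The loss is modest for a continuous outcome (step 6 of the working). It will be larger for sparse outcomes: SYNTAX above 32 was seen in 34 of 596 patients so far (5.7%), and the number of MACCE is not yet known. The loss for those outcomes has not been calculated here.

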#### Endpoints

The study primarily aims to combine clinical characteristics with established and novel biomarkers, in order to develop a risk prediction model, which could optimally identify patients at high risk for CAD and most importantly, patients at high risk for complex CAD based on their metabolite signatures.

A secondary endpoint of this study is the identification of a biomarkers’ panel for the distinction of acute from chronic coronary syndromes by detecting metabolite pattern differences. Finally, all patients will be followed-up via telephone for 12 months for any MACCE to develop a new prognostic metabolomics-based model for CAD patients (Fig. 1).

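### The 12-month MACCE model is to be built by significance-based predictor selection from at least 23 candidate biomarkers with no shrinkage stated, so its predicted risks would likely be too extreme

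*Protocol article*

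**What the plan says.** The Endpoints section lists the MACCE model last, after the primary and secondary aims: telephone follow-up for 12 months is meant "to develop a new prognostic metabolomics-based model for CAD patients".

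The Statistical analysis section gives the route: "Univariable, multivariable and correlations analysis will be carried out to clarify independent predictors of various CAD characteristics". The same sentence goes on to cover biomarkers taken one at a time and follow-up MACCE. Significance is set at 0.05 and all tests are run in SPSS v. 26. Cox regression is the only time-to-event regression named; it is mentioned for the SYNTAX groups and for checking models that emerge. Bootstrapping is mentioned only for the linear and logistic models, to deal with non-parametric data. No penalty, shrinkage or optimism correction is named.

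The Biochemical analysis section names the measurements. It begins its targeted list with "The quantification of four ceramide species" and adds fifteen acylcarnitines and four protein markers (galectin-3, adiponectin, NGAL, ApoB/ApoA-I). Ceramide ratios, fatty acids and untargeted compounds are also measured, without a count.

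The Sample size estimation section works only on the SYNTAX regression: "In this pilot study we chose 10 predictors", and "So for an A of 0.01 and a Power of 0.95 a sample size of 1014 is sufficient". In that context it also states the aim of using fewer than 10 predictors in the main study. No MACCE rate or event count appears anywhere.

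**The concern.** A model whose predictors are picked by significance from a long list, and whose coefficients are then used as estimated, is over-fitted. Its linear predictor is too spread out, so in new patients the calibration slope falls below 1: high predicted risks are too high and low ones too low. The fewer the events per candidate, the worse this is. The number that matters is the number of candidates screened, not the number left in the final model.

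The Background section gives the study's ultimate goal as a clinical tool for picking out patients at high risk of adverse cardiovascular events. The checks named in the Statistical analysis section (ROC curve and AUC, Kaplan–Meier, log-rank) measure separation of risk groups, not agreement between predicted and observed risk. They would not reveal this fault.

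**Working it through.** **1. The plan's own figure.** Inputs from Sample size estimation: pilot n = 100, R² = 0.370, 10 predictors, H0 ρ² = 0.20, H1 ρ² = 0.30, alpha 0.01, power 0.95.
- Adjusted pilot R² = 1 − (1 − 0.370) × 99/89 = 0.299, which matches the 0.30.
- The exact test of R² with random predictors gives N = 1014 two-sided (power 0.950) and 900 one-sided, so the stated 1014 reproduces as a two-sided test.
- 1014 × 1.05 = 1064.7, hence 1065.

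The figure is right for the SYNTAX regression. It says nothing about MACCE.

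**2. Candidates.** 4 ceramides + 15 acylcarnitines = 19 metabolites; + 4 protein markers = 23. Ratios, fatty acids, untargeted compounds and clinical variables come on top.

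**3. Events (assumed rates).** Patients followed: 1065 × 0.95 ≈ 1012.

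| Assumed 12-month MACCE | Events | Events per candidate (23) |
|---|---|---|
| 5% | 51 | 2.2 |
| 10% | 101 | 4.4 |
| 20% | 202 | 8.8 |

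**4. Expected shrinkage.** The relation is p = n(S − 1) ln(1 − R²/S), where p is the number of candidate parameters, S the expected shrinkage, and R² the Cox–Snell value. R² is taken as an assumed share of its maximum, 1 − exp{2[r ln r + (1 − r) ln(1 − r)]} for event rate r. With n = 1012:

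| Rate | Max R² | p allowed at S = 0.9 (15% / 25% of max) | S with 23 candidates (15% / 25%) |
|---|---|---|---|
| 5% | 0.328 | 5.7 / 9.7 | 0.69 / 0.79 |
| 7.5% | 0.413 | 7.2 / 12.3 | 0.74 / 0.83 |
| 10% | 0.478 | 8.4 / 14.4 | 0.77 / 0.85 |
| 20% | 0.632 | 11.3 / 19.6 | 0.82 / 0.89 |

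Example, 5% and 15%: R² = 0.15 × 0.328 = 0.0492; p = 1012 × (−0.1) × ln(1 − 0.0492/0.9) = 5.7. In every row 23 exceeds the limit.

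**5. Simulation.** Calibration slope in new patients; the ideal is 1.

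*Cox, N = 1014, 23 candidates, 5 true predictors, correlation 0.3, screening at p < 0.05 capped at 9 predictors:*

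| Events | All 23 fitted (log HR 0.2 / 0.1 per SD) | Screened, at most 9 (0.2 / 0.1) |
|---|---|---|
| about 50 | 0.50 / 0.18 | 0.76 / 0.43 |
| about 100 | 0.66 / 0.26 | 0.85 / 0.48 |
| about 200 | 0.77 / 0.50 | 0.91 / 0.75 |

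A repeat run of the 50- and 100-event settings differed by up to 0.10.

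*Logistic approximation, 31 candidates in correlated blocks, univariable then backward selection at 0.05:* 0.59 (50 events) and 0.72 (100 events) with many weak effects; 0.73 and 0.87 with few strong effects. Ridge on the same data gave 1.05–1.15. AUC, selected model against ridge, was 0.64 against 0.67 and 0.67 against 0.68 with weak effects, and 0.69 against 0.69 and 0.71 against 0.70 with strong effects.

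*A further simulation, 23 candidates with selection at 0.05:* mean slopes 0.67–0.80 at 5%, 0.78–0.84 at 10% and 0.85–0.89 at 20% MACCE.

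**The case against.** **The method is partly inferred.** A reader might infer that the article commits to an unpenalised Cox model for developing the MACCE score. It does not say so: Cox is assigned to the SYNTAX groups and to checking models. A full protocol or analysis plan could add a penalty. This stands as a limit on the wording. What the article does state is predictor identification for MACCE by univariable and multivariable analysis at 0.05, and that is what produces the optimism.

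**The candidate list is an assay list.** Nothing says that every measured item will be tried against MACCE, and the aim of fewer than 10 predictors could be read as a biology-led choice. But that aim is stated for the SYNTAX models, while the analysis section takes biomarkers individually. Carried over to MACCE, a cap of 9 after screening raises the slopes but leaves them below 1 in every setting simulated. It would also be wrong to speak of 23 metabolites: 4 of the 23 are proteins.

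**The size rests on assumptions.** No event rate is given, and MACCE includes revascularisation in a cohort with about 45% acute coronary syndrome, so the rate could exceed 10%. With few strong effects and 100 events the slope is 0.87. This stands for the size but not for the direction, which holds up to 20%.

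**The gain is limited.** The goal is worded as distinguishing high-risk patients, which is discrimination, and AUC hardly changes. Ridge also errs slightly in the other direction (1.05–1.15). Both points stand.

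**Study size.** A reader might infer that 1014 is wrong or that the trial must be enlarged. Neither follows: 1014 reproduces for its own purpose, and the remedy is a different fit on the same patients.

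**Conclusion.** The point holds in a limited form. Followed as written, the route to the MACCE model would likely give predicted risks that are too extreme. At an assumed 5–10% MACCE rate, expected shrinkage with the 23 countable candidates is about 0.69–0.77 at 15% of maximum R² and 0.79–0.85 at 25%. Slopes after selection are mostly about 0.6–0.87, and below 0.5 in the Cox simulation with weak effects (log HR 0.1). The direction survives a 20% rate.

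This rests on three things outside the text: the event rate, the strength of the true effects, and the inference that no shrinkage will be applied because none is named. The fault concerns calibration. The documents and calculations do not support a claim that discrimination would be materially worse.

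**What to change.** In Statistical analysis and Endpoints, state that:

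- the MACCE model will be fitted by penalised (ridge or elastic-net) Cox regression, or its coefficients will be multiplied by a bootstrap shrinkage factor, with the whole selection process repeated in each bootstrap sample;
- the optimism-corrected calibration slope will be reported alongside the AUC;
- the number of candidate parameters will be judged against the observed number of events before fitting.

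A short prespecified predictor list is one option, not a requirement. It lowers the optimism, but at 5% MACCE and 15% of maximum R² even nine fixed predictors have an expected shrinkage of 0.85. It would also push metabolites left off the list into an exploratory search.

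Cost: a few sentences, a little more analysis work, and software beyond SPSS v. 26. No extra patients or measurements are needed.
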